### Sample size

The sample size is calculated based on data from a recently published cohort study on pelvic floor rehabilitation in fecally incontinent patients [31]. Patients who reported their situation to be better after pelvic floor rehabilitation showed a mean improvement score of 4.33 points on the Vaizey score and patients who rated their situation to be equal or (much) worse showed a mean improvement score of one point (baseline average Vaizey score is 18). As subjective improvement can not be projected as decimals on the Vaizey score, we calculated two sample sizes: (1) with exact scores and (2) with absolute scores to correspond with the Vaizey score and estimate of the minimally important change (MIC). The absolute difference in improvement of four points between the patients who rated themselves to be better and the patients who rated themselves to be equal or (much) worse is considered the MIC on the Vaizey score between both trial arms [31].

The first sample size is calculated using an average Vaizey score of 13.67 and a standard deviation of 8.45 for sample 1 and an average Vaizey score of 17 and a standard deviation of 3.90 for sample 2, which resulted in a sample size of 106 patients. The second sample size is calculated using an average Vaizey score of 13 and a standard deviation of 8.45 for sample 1 and an average Vaizey score of 17 and a standard deviation of 3.90 for sample 2, which resulted in a sample size of 73 patients. The sample size is in a range of 73 to 106 patients and we decided to include at least 106 patients to feel confident about the required sample size.

All calculations assume a one-sided effect (first trial arm has a better outcome than second trial arm), an alpha of 0.05, a power of 80% and an expected drop-out of 10%. It is expected that the drop-out will be minimal since patients will be greatly motivated to participate and adhere to the protocol, by experiencing such an embarrassing and socially restricting disorder.

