### Data analysis

In case of longitudinal missing data, imputation is performed with the last observation carried forward method. Main outcome is tested according to the intention to treat principle. Both treatment groups are checked for comparability regarding baseline data. An independent t-test is done for continuous variables and a Chi-square test for categorical variables. Analyses are performed to compare differences within groups between baseline and short-term follow-up (3 months) and long term follow-up (6 and 12 months) regarding primary and secondary outcome measures. A subgroup analysis is done for the patients with and without co-interventions. Analysis of variance is used to determine the difference in mean change of outcome measure between clinical subgroups. A two-tailed p-value of 0.05 is considered to indicate statistical significance. Data analysis is done using SPSS version 13.0 (SPSS, Inc., Chicago, Illinois). Confounders that are taken into account are presence of urinary incontinence, use of anal tampons, compliance and medication use.

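### The sample size rests on a one-sided 5% test but the analysis is two-tailed at 5%, so 106 patients give about 70–74% power, not 80%, for the 3.33-point difference that produced 106

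*Protocol article*

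**What the plan says.** The Sample size section of the protocol article gives two calculations with the same standard deviations and different means.

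- Exact scores: "The first sample size is calculated using an average Vaizey score of 13.67 and a standard deviation of 8.45 for sample 1", against "an average Vaizey score of 17 and a standard deviation of 3.90 for sample 2, which resulted in a sample size of 106 patients".
- Rounded scores: "The second sample size is calculated using an average Vaizey score of 13 and a standard deviation of 8.45 for sample 1", against "an average Vaizey score of 17 and a standard deviation of 3.90 for sample 2, which resulted in a sample size of 73 patients".

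The larger total was taken: "we decided to include at least 106 patients to feel confident about the required sample size". The basis of both calculations is one sentence: "All calculations assume a one-sided effect (first trial arm has a better outcome than second trial arm), an alpha of 0.05", continuing with "a power of 80% and an expected drop-out of 10" per cent.

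The Data analysis section then fixes the criterion for the results: "A two-tailed p-value of 0.05 is considered to indicate statistical significance". It reserves no separate criterion for the primary outcome. The Study design section states a directional hypothesis (a larger reduction with combined training), but nowhere does the article provide for a one-sided test.

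**The concern.** A two-tailed 5% test allows only 2.5% in the hypothesised direction, so the planned test is stricter than the one used to size the trial. If 106 came from the one-sided alpha, the 80% attached to it does not describe the planned analysis.

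Two things are at stake. A non-significant result would be read as coming from a trial with a 20% chance of missing its target difference, when on the plan's inputs that chance is nearer 26% to 30%. And while both statements stand, a primary result in the expected direction with a two-tailed p between 0.05 and 0.10 meets the sizing criterion but fails the analysis criterion, which leaves room for argument after the data are seen.

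**Working it through.** **Inputs.** From Sample size: SDs 8.45 and 3.90; differences 17 − 13.67 = 3.33 and 17 − 13 = 4; 80% power; 10% drop-out; alpha 0.05 one-sided (z = 1.645). From Data analysis: 0.05 two-tailed (z = 1.960). Equal allocation is assumed (two arms, blocks of four, no ratio stated). The normal approximation is used for a two-group comparison of means.

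**Step 1: reproduce the plan's totals.**

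n per arm = (8.45² + 3.90²)(z_alpha + z_power)² / d², where 8.45² + 3.90² = 71.40 + 15.21 = 86.61.

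One-sided: (1.645 + 0.842)² ≈ 6.18.
- d = 3.33: 86.61 × 6.18 / 11.09 ≈ 48.3 per arm. Rounded to 48: 48 × 2 × 1.1 = 105.6, so 106, as stated.
- d = 4: 86.61 × 6.18 / 16 ≈ 33.5 per arm (33.47). Rounded to 33: 33 × 2 × 1.1 = 72.6, so 73, as stated.

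**Step 2: same inputs, two-sided.** (1.960 + 0.842)² ≈ 7.85.
- d = 3.33: 61.3 per arm, about 123 evaluable; × 1.1 ≈ 135. With whole patients per arm (62, total 124) and division by 0.9, the total is 138.
- d = 4: 42.5 per arm, 85 evaluable; × 1.1 ≈ 93.5.

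Neither 106 nor 73 comes from a two-sided alpha.

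**Step 3: power of the planned two-tailed test.**

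Power = Φ(d / SE − 1.960), with SE = √(86.61 / n per arm).

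106 randomised with 10% lost leaves 95.4 evaluable, or 47.7 per arm: SE = √(86.61 / 47.7) = 1.348.
- d = 3.33: Φ(2.471 − 1.960) = Φ(0.511) = 0.695.
- d = 4: Φ(2.968 − 1.960) = Φ(1.008) = 0.843.

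All 106 analysed, 53 per arm: SE = √(86.61 / 53) = 1.278.
- d = 3.33: Φ(2.605 − 1.960) = Φ(0.645) = 0.741.
- d = 4: Φ(3.129 − 1.960) = Φ(1.169) = 0.879.

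Check on the plan's own basis: with 47.7 per arm and z = 1.645, d = 3.33 gives Φ(0.826) = 0.796, which is the stated 80%.

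| Randomised | Difference | Two-sided power, 10% lost | Two-sided power, all analysed |
|---|---|---|---|
| 106 | 3.33 | 70% | 74% |
| 106 | 4 | 84% | 88% |
| 73 | 4 | 69% | 74% |

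For the last row, 65.7 evaluable gives 0.693 and 73 evaluable gives 0.738. Noncentral-t calculations lower these figures by about one to two percentage points.

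**The case against.** The strongest reply is that the Sample size section names 4 points as the minimally important difference between the arms, and at 4 points 106 patients exceed 80% power even two-sided. That is correct as arithmetic. A reader might infer that 106 patients cannot deliver 80% power in any scenario, and the article does not support that.

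As a defence of the stated power, though, the 4-point figure is weak. The improvements it is drawn from, 4.33 and 1, differ by 3.33; the rounded decreases of 4 and 1 under Secondary goals differ by 3. And 106 was derived from the 3.33-point calculation, not the 4-point one.

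A reader might also infer that the true power is 70%. That is too firm. It assumes about 95 evaluable patients, whereas the plan combines intention to treat with last observation carried forward and expects minimal drop-out, so up to 106 may be analysed. Carrying values forward could in turn dilute the difference. The SDs and means also come from patients grouped by self-rated outcome in a cohort, not from trial arms. The defensible statement is a range on the plan's own inputs.

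Finally, the mismatch errs on the cautious side: a two-tailed test neither inflates the type I error nor biases the estimate. That stands, and it limits the harm to misstated power and an unsettled criterion. Baseline adjustment might recover some power, but neither section assumes it.

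**Conclusion.** The contradiction is explicit, and both totals confirm it. For the 3.33-point difference that produced 106, the planned two-tailed test has about 70% power after 10% drop-out and about 74% with everyone analysed, against the stated 80%. For 4 points, 106 patients still suffice (84% to 88%), while the lower figure of 73 does not (69% to 74%). The results rest on the plan's means and SDs taken as given, equal allocation, exactly 106 randomised (the plan sets this as a minimum), and a two-group comparison of means of the kind used for sizing. The arithmetic in the article is sound on its one-sided basis; the error is attaching its 80% to a trial that will be tested two-tailed.

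**What to change.** Keep the two-tailed 0.05 criterion and the target of at least 106. In Sample size, label the 106 and 73 derivations as one-sided and add: *With 106 randomised, the two-sided 5% test has about 70–74% power for 3.33 points and 84–88% for 4 points.* Give the 3.33-point figure as the headline, since it is the difference that the article's own improvements imply.

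Do not simply delete the one-sided sentence. It also carries the alpha, the power and the drop-out allowance, and without it 106 and 73 would stand with no basis and could not be reproduced under a two-sided test.

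The cost is wording only, made before any unblinded analysis, and a less favourable stated power. If the sponsor wants 80% two-sided for 3.33 points, the alternative is about 135 to 138 randomised, which is 29 to 32 more; at the article's expected one inclusion a week, that is roughly 29 to 32 more weeks of recruitment. Prespecifying and justifying a one-sided primary test would also reconcile the two sections, but it would replace the stricter criterion already stated.

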### Referral

After diagnosis and inclusion, patients are referred to an extramural private practice, preferably nearby their home address. Private practices are selected with physiotherapists experienced in women's health, who are registered at the Dutch Society for Physical Therapy in Pelvic Floor Disorders and Pre- and Postnatal Healthcare (NVFB). They are all educated and trained in the performance of invasive techniques, as is used during digital testing and RBT. In total, 90 physiotherapists participate throughout the Netherlands. The initial physiotherapy session should be within three weeks after referral. The patient hands over an acknowledged doctor's referral letter and fifteen rectal balloons (group 1) to the physiotherapist before the initial session. FI is not recognized as a chronic disorder and insurance coverage is patient dependent. However, physiotherapy in this trial is considered as being part of usual care, as included patients would also be excellent candidates for physiotherapy outside the scope of this trial. Since January 2006 a referral letter is not obligatory anymore.

### Physiotherapy intervention

Treatment is administered according to a standardized protocol, which has been developed by clinicians and physiotherapists specialized in the field of pelvic floor disorders. Physiotherapy consists of pelvic floor muscle training (PFMT) and rectal balloon training (RBT; only trial arm one). Patients receive 12 sessions within three months after the initial session, starting with two sessions a week during three weeks, and thereafter reducing to one session a week. The first session takes 45 minutes and all subsequent sessions 35 minutes. A case report form physiotherapy (CRF) is filled out for each physiotherapy session.

Physiotherapists are aware of details about the medical history, physical examination and diary, but blinded for findings of anal manometry, rectal capacity measurement, anorectal sensation, anal endosonography, defecography, FIQL and PREFAB-score. During physiotherapy sessions, information is obtained by performing peri-anal inspection, digital rectal evaluation and rectal balloon training (trial arm 1).

### Pelvic floor muscle training

PFMT is offered to all included patients and consists of selective voluntary contractions and relaxations of the pelvic floor muscles and the anal sphincter. Awareness of these muscles is necessary, as is the avoidance of the use of surrounding muscles like the adductors or abdominals. PFMT aims at maximizing strength, improving duration of strength, and improving timing and coordination of contractions. One treatment cycle starts with a series of 8–12 single maximum contractions, sustained for 1–3 seconds. During treatment the series are extended from 1–3, and the sustained maximum contraction from 1–3 seconds to 6–8 seconds. A one-minute rest is allowed between the cycles. One cycle is repeated three times. Furthermore, patients perform three sustained submaximal contractions of 30 seconds, with one-minute rest in between. Patients are also instructed to perform home exercises daily. At home the cycles and sustained contractions are done in the same way and three times daily. The exercises are practiced in different starting positions and circumstances, simulating as much as possible daily life. Patients' compliance is encouraged because the home exercises determine to a great extent the success of physiotherapy. Digital rectal examination is used to measure the ability of pelvic floor muscles to contract and to quantify the strength. A contraction is considered to be sufficient if the pelvic floor and anal sphincter lift inward.

### Rectal balloon training

A rectal balloon attached to a syringe is introduced in the rectum and slowly inflated with air to imitate rectal contents. Sensory threshold, urge sensation, and maximal tolerated volume are assessed. Patients with an insensitive rectum are trained to discriminate and respond to smaller rectal volumes of distension until a normal level of sensory threshold is reached or further improvement cannot be expected. In this way, patients receive an earlier warning from stool entering the rectum and impending defecation. In addition, patients can counteract reflex inhibition of the internal sphincter due to awareness of stool in the rectum [15]. Patients with a hypersensitive rectum are trained to tolerate larger volumes by the use of progressive distension and urge resistance until a normal level of urge sensation is reached or the urge does not diminish with time or is uncomfortable. Patients with weakness of the pelvic floor muscles learn to contract these muscles immediately and strongly in response to rectal filling.

### Details of each session

Details of each physiotherapy session are presented in Additional file 1: Details of each physiotherapy session.

### Co-interventions

After three months follow-up the physician evaluates the Vaizey score and the GPE-score. In case of an improvement of less than four points on the Vaizey score and/or a GPE-score of eight or nine, the clinician decides upon further therapeutic steps. If necessary, co-interventions are allowed after three months follow-up, although this should be avoided as much as possible. Examples of co-interventions are sacral nerve stimulation, anal repair or lavage. During physiotherapy treatment, patients are not allowed to use anal tampons.

The most common used drugs in patients with moderate to severe FI are Loperamid and sometimes Norit. Medical interventions and/or diet changes are first tried in the conservative management of patients with FI. If patients do not benefit from medical interventions, usual care implies referral for physiotherapy interventions. So, the majority of patients do not use drugs before physiotherapy management since they appeared not to be helpful. Nevertheless, patients who use drugs before starting with physiotherapy interventions are instructed to follow an unchanged stable medical regimen. Therefore, ongoing and change in medication use are monitored during the trial. In the analysis we will account for co-interventions, such as medication use.

### Data analysis

In case of longitudinal missing data, imputation is performed with the last observation carried forward method. Main outcome is tested according to the intention to treat principle. Both treatment groups are checked for comparability regarding baseline data. An independent t-test is done for continuous variables and a Chi-square test for categorical variables. Analyses are performed to compare differences within groups between baseline and short-term follow-up (3 months) and long term follow-up (6 and 12 months) regarding primary and secondary outcome measures. A subgroup analysis is done for the patients with and without co-interventions. Analysis of variance is used to determine the difference in mean change of outcome measure between clinical subgroups. A two-tailed p-value of 0.05 is considered to indicate statistical significance. Data analysis is done using SPSS version 13.0 (SPSS, Inc., Chicago, Illinois). Confounders that are taken into account are presence of urinary incontinence, use of anal tampons, compliance and medication use.

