▪ PREFAB-score: the PREFAB-score is a modified version of the widely used and accepted PRAFAB-score in the urinary incontinence field. The PRAFAB-score is a simple and quickly obtained score which summarizes several objective and subjective components of the severity of urinary incontinence complaints (ranging from 5–20) [33]. The score has proven to be reliable, valid and responsive [34]. Since most of the PRAFAB-score, except for the "amount" item, is applicable to fecally incontinent patients as well, it is suggested to adapt the PRAFAB-score to fecally incontinent patients. From the patients' point of view, two aspects about excretion of feces are reported to be highly embarrassing and affecting social life and body image: whether the excretion can be held up by a pad or not and whether excretion can be smelled by the environment or not. These two aspects, reflecting social limitations, are therefore integrated in the modified PRAFAB-score (min-max = 6–20; range = 15).

▪ Global perceived effect (GPE) (Table 2): this subjective score reflects the change in complaints after physiotherapy treatment compared to the period before treatment and ranges from 1–9 points. A score of 8 or 9 indicates much worsening of complaints and is an indication to consider co-interventions.

**Table 2 T2:** Global perceived effect (GPE-score)

To which degree have your complaints changed compared to the period before physiotherapy treatment?
At the moment, the complaints are .....
1. Very much improved
2. Much improved
3. Moderately improved
4. Slightly improved
5. Unchanged
6. Slightly worse
7. Moderately worse
8. Much worse
9. Very much worse
..... compared to the period before physiotherapy treatment

Follow-up measurements are scheduled at 3, 6 and 12 months after inclusion. Primary outcome measure is the Vaizey score [28]. Success after physiotherapy is defined as a reduction in Vaizey score of more than four points (16.7%) compared to baseline measurement. Recently, it is reported that patients who rated their situation to be better, improved four points on the Vaizey score [31]. Secondary outcome measures are anorectal resting and squeeze pressure, rectal capacity, anorectal sensation, diary results, FIQL, PREFAB-score and GPE-score.

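### Last observation carried forward is the only missing-data method named; it implies zero change for patients lost before month 3 and can bias the arm difference either way, modestly at the planned 10% drop-out

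*Protocol article*

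**What the plan says.** The Data analysis section sets the rule: "In case of longitudinal missing data, imputation is performed with the last observation carried forward method". The next sentence sets the analysis principle: "Main outcome is tested according to the intention to treat principle". The section gives no second method, no assumption about why data are missing and no sensitivity analysis.

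The outcome schedule is in Baseline and follow-up measurements: "Follow-up measurements are scheduled at 3, 6 and 12 months after inclusion". The primary outcome is the Vaizey score (0 to 24), and the same section adds a responder definition: "Success after physiotherapy is defined as a reduction in Vaizey score of more than four points (16.7%) compared to baseline measurement".

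The Sample size section allows for "an expected drop-out of 10" per cent and expects actual loss to be minimal. The Co-interventions section permits further treatment after the 3-month assessment, mainly for patients who have improved too little.

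**The concern.** No Vaizey follow-up is scheduled between baseline and month 3. Under intention to treat, a patient lost in that interval can only carry the baseline score, which gives a change of exactly zero and counts as a failure on the responder definition. A patient lost later is assumed to stay at the 3- or 6-month score, although the plan lets treatment change after month 3.

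The filled-in scores are then analysed as if they had been measured. Two things are at stake. One is the estimate, which is pulled towards zero by equal loss and shifted by unequal loss. The other is its standard error, which does not reflect that some outcomes were never seen. The method is a stated choice in the article, so this is not a detail left to a fuller document.

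**Working it through.** **Inputs from the Sample size section**
- Mean improvement 4.33 points (sample 1) and 1 point (sample 2) from a baseline of 18, hence "an average Vaizey score of 13.67 and a standard deviation of 8.45 for sample 1"; the second sample has mean 17 with SD 3.90. The planning difference is 17 − 13.67 = 3.33.
- One-sided alpha 0.05, power 80%, drop-out 10%, total 106.

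**Assumptions, not in the documents**
- 53 patients per arm (blocks of four are stated, the allocation ratio is not).
- The planning SDs apply to the change score.
- All loss occurs before month 3.
- Drop-outs would have improved like completers.
- The unequal splits are illustrations.

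**Step 1: reproduce the plan's figure.** n per arm = (1.645 + 0.842)² × (8.45² + 3.90²) / 3.33² = 48.29. The total is 96.6, and × 1.1 gives 106.2 (÷ 0.9 gives 107.3). The stated 106 is reproduced, so the inputs are read as the plan meant them.

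**Step 2: expected estimate under LOCF.** Let d1 and d2 be the shares lost in the combined arm and on PFMT alone, each entering with zero change:

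E = 4.33(1 − d1) − 1.00(1 − d2)

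**Step 3: standard errors.** With mean improvement m in an arm, the variance of the filled-in changes is (1 − d)SD² + d(1 − d)m².
- LOCF SE = √[(v1 + v2)/53]
- Observed-data SE = √[8.45²/(53(1 − d1)) + 3.90²/(53(1 − d2))]

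For 10% in each arm:
- v1 = 0.9 × 71.40 + 0.09 × 18.75 = 65.95
- v2 = 0.9 × 15.21 + 0.09 × 1 = 13.78
- LOCF SE = √(79.73/53) = 1.227
- Observed-data SE = √(71.40/47.7 + 15.21/47.7) = 1.348

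| Lost, combined / PFMT alone | LOCF estimate (true 3.33) | Bias | LOCF SE | Observed-data SE | Two-sided power, LOCF / observed |
|---|---|---|---|---|---|
| 10% / 10% | 3.00 | −0.33 | 1.227 | 1.348 (LOCF 9% smaller) | 68.6% / 69.5% |
| 15% / 5% | 2.73 | −0.60 | 1.210 | 1.374 (12% smaller) | 61.7% / 67.9% |
| 5% / 15% | 3.26 | −0.07 | 1.242 | 1.325 (6% smaller) | 74.8% / 71.0% |
| 20% / 20% | 2.66 | −0.67 | 1.169 | 1.429 (18% smaller) | 62.5% / 64.4% |

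**Step 4: no true difference, both arms improving by m.** The false difference is m(d2 − d1), positive values favouring the combined arm.

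| m | Lost, combined / PFMT alone | False difference | Two-sided type I error |
|---|---|---|---|
| 4.33 | 10% / 10% | 0 | 0.050 |
| 4.33 | 5% / 15% | 4.33 × 0.10 = 0.43 | 0.064 |
| 4.33 | 0% / 20% | 4.33 × 0.20 = 0.87 | 0.104 |
| 1 | 5% / 15% | 0.10 | 0.051 |
| 1 | 0% / 20% | 0.20 | 0.053 |

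The effect of carrying a 3- or 6-month score to later visits is not quantified, because the article gives no planning figures for change after month 3.

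**The case against.** **Size.** At the planned drop-out, split equally, the estimate and its standard error shrink almost in step: 3.00/1.227 = 2.44 against 3.33/1.348 = 2.47. Power barely moves and type I error holds. The false 0.43 points is about a tenth of the plan's 4-point minimally important change. This stands and limits the weight of the point.

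**Assumptions.** The 10% is total drop-out with no timing, and the 15%/5% splits have no source. The 4.33 and 1 come from patients in a cohort grouped by self-rated improvement, not from trial arms. If early leavers in truth gain little, zero change is near the truth and there is little dilution. This also stands, so the figures are illustrations under declared assumptions.

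Four stronger readings are tempting but not supported:
- *The plan says baseline is carried forward.* It does not. That is inferred from the rule, the intention-to-treat principle and the visit schedule.
- *The smaller standard error means too many false positives.* With equal loss and no true difference, type I error stays at 0.05. Only unequal loss raises it in these calculations.
- *The balloon arm will lose more patients, and LOCF will then flatter it.* The Blinding section confirms that patients are unblinded and only one arm has balloon training. But the Relevance section says no adverse events have been reported for either treatment, digital rectal examination is used in both arms, and the article predicts no unequal loss. More loss in the combined arm would in any case bias against it.
- *Inflating the sample for drop-out contradicts imputing the drop-outs.* Recruiting extra patients is compatible with imputation, so this is not a contradiction.

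**Conclusion.** The point holds in a limited form. LOCF is a poor choice as the sole missing-data method. It rests on no later change in any drop-out, implies zero change for those lost before month 3, and treats imputed scores as observed.

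At 10% overall loss the bias in the planning difference runs from −0.07 to −0.60 points over the splits tried, with a standard error 6% to 12% below the observed-data value. With equal loss the practical effect on the test is negligible. The risk lies in unequal loss, and its direction depends on which arm loses more, so LOCF cannot be defended as reliably conservative. All these figures assume that every loss is before month 3 and that drop-outs would have done as well as completers. The plan should be changed because a better analysis costs little, not because the trial's conclusion is shown to be in danger.

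**What to change.** Replace LOCF in the main between-arm analysis of the Vaizey score by one of the following:
- a likelihood-based repeated-measures model on all observed scores (baseline, 3, 6 and 12 months), with baseline in the outcome vector. If baseline is only a covariate, a patient lost before month 3 has no outcome record and contributes nothing;
- multiple imputation carried out by arm, with baseline Vaizey in the imputation model.

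In either case, keep all patients as randomised and report the arm contrast at the trial's designated primary time point. The article does not single out one visit, so that must be stated. Add a sensitivity analysis for data not missing at random, for example giving drop-outs progressively worse outcomes by arm. Keep LOCF at most as a further sensitivity analysis.

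The cost is a change of wording and slightly more programming, with no extra visits or patients. The main analysis would then rely on data being missing at random, which cannot be tested and is why the added sensitivity analysis is needed.
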